**Safety** **evaluation**

Any adverse events (defined as any functional lesion caused by the intervention, such as knee joint or ankle sprain, knee soreness, lumbar muscle strain and so on) will be recorded on case report form (CRF) during intervention period. If any adverse event occurs, the coaches or project managers will provide the corresponding treatment to the participant. The adverse events will be immediately reported to the primary investigator and ethics committee to decide if the participant needs to withdraw the trial.

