**Control group**

No specific exercise will be administered on the participants in control group. They will be informed to maintain their original lifestyle.

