**Intervention regimen**

The intervention period in this trial will last 12 weeks. All participants will be required to record physical activity diaries including the type and intensity of physical activity or exercises, as well as the sedentary time, sleeping time everyday throughout this study.

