**Follow-up period**

During the 12-week follow-up period, all of the participants will return to their original lifestyles, but be required to record their daily physical activities or sport information. The primary outcomes will be re-measured at end of follow-up period.

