**Recruitment**

**Allocation and intervention**

**Follow up**

**Analysis**

**Figure 1 Flow diagram of participants**

| **Table 1 Trial Processes Chart**   | Items | Before enrollment (week) | TCC training phase(week) | Training end (week) | Follow-up (week) | Follow-up end(week) | | --- | --- | --- | --- | --- | --- | | **-2-(-1)** | **1-12** | **13** | **13-24** | **25** | | Inclusion criteria | * |  |  |  |  | | Exclusion criteria | * |  |  |  |  | | Informed consent | * |  |  |  |  | | Baseline | * |  |  |  |  | | Randomization | * |  |  |  |  | | Self-esteem | * |  | * |  | * | | Mood and mindfulness | * |  | * |  | * | | Self-efficiency | * |  | * |  | * | | Psychological symptom score | * |  | * |  | * | | Stress test | * |  | * |  | * | | Flexibility | * |  | * |  | * | | Step testing | * |  | * |  | * | | Rest heart rate | * |  | * |  | * | | Vital Capacity | * |  | * |  | * | | Systolic [blood](app:ds:blood) [pressure](app:ds:pressure) | * |  | * |  | * | | [Diastolic](app:ds:diastolic) [blood](app:ds:blood) [pressure](app:ds:pressure) | * |  | * |  | * | | Balance | * |  | * |  | * | | [Lower](app:ds:lower) [limbs](app:ds:limbs) proprioception | * |  | * |  | * | | Attention span | * |  | * |  | * | | Quality of life | * |  | * |  | * | | Quality of sleep | * |  | * |  | * | | Safety outcomes |  | * |  | * |  | | Self-report diaries |  | * |  | * |  | |
| --- | --- | --- | --- | --- | --- | --- | --- | --- | --- | --- | --- | --- | --- | --- | --- | --- | --- | --- | --- | --- | --- | --- | --- | --- | --- | --- | --- | --- | --- | --- | --- | --- | --- | --- | --- | --- | --- | --- | --- | --- | --- | --- | --- | --- | --- | --- | --- | --- | --- | --- | --- | --- | --- | --- | --- | --- | --- | --- | --- | --- | --- | --- | --- | --- | --- | --- | --- | --- | --- | --- | --- | --- | --- | --- | --- | --- | --- | --- | --- | --- | --- | --- | --- | --- | --- | --- | --- | --- | --- | --- | --- | --- | --- | --- | --- | --- | --- | --- | --- | --- | --- | --- | --- | --- | --- | --- | --- | --- | --- | --- | --- | --- | --- | --- | --- | --- | --- | --- | --- | --- | --- | --- | --- | --- | --- | --- | --- | --- | --- | --- | --- | --- | --- | --- | --- | --- | --- | --- | --- | --- | --- | --- | --- | --- | --- | --- | --- | --- | --- |

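### Causation by Tai Chi is built into the adverse-event definition, so control events cannot be counted and no excess risk can be estimated; the recording window also conflicts with Table 1.

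*Protocol*

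**What the plan says.** The Safety evaluation section of the protocol covers adverse events "defined as any functional lesion caused by the intervention" and gives sprains, a sore knee and back strain as open-ended examples. It says that they "will be recorded on case report form (CRF) during intervention period". The Intervention regimen section fixes that period: "The intervention period in this trial will last 12 weeks". The follow-up is a separate phase: "During the 12-week follow-up period, all of the participants will return to their original lifestyles". On the comparator, the Control group section says: "No specific exercise will be administered on the participants in control group".

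When an event occurs, "the coaches or project managers will provide the corresponding treatment to the participant", and the event is "reported to the primary investigator and ethics committee to decide if the participant needs to withdraw the trial". The Blinding section says that coaches cannot be blinded, that the project manager holds the allocation sequence, and that neither takes part in outcome assessment.

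Figure 1 lists safety among the outcomes assessed after the intervention in a two-group flow. In Table 1, the row "Safety outcomes" is marked under the training phase (weeks 1-12) and again under follow-up (weeks 13-24).

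**The concern.** Whether a treatment caused an event is normally a judgement recorded about an event that has already been captured. Here it is a condition for the event to be captured at all. That removes the one thing a randomised control group adds to safety data, which is the rate of the same complaints without the treatment. The protocol's own examples are complaints that a person can have without doing Tai Chi, so a count in the Tai Chi group alone cannot be read as harm or as its absence. No later analysis plan can repair this, because the control events would never have been written down.

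The second matter is a plain inconsistency. The text and Table 1 give different periods for collecting safety data, so sites cannot follow both.

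**Working it through.** The protocol gives no safety figure to reproduce, so the check sets the sections side by side. A short illustration follows.

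**1. Can a control have an adverse event?**
- Condition in Safety evaluation: the lesion was caused by the intervention.
- Control group section: no exercise is given.
- It follows that a lesion in a control cannot qualify. The only theoretical exception is a control who takes up Tai Chi, and doing so regularly is itself listed under Withdrawal criteria.
- The recorded control count is therefore 0 by construction.

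**2. Who judges causation?**
- Coaches or project managers: treatment of the participant.
- Primary investigator and ethics committee: decision on withdrawal.
- Judgement that an event was caused by the intervention: no one is named.
- The coaches and the project manager know the allocation, and the judgement itself can hardly be made without knowing it.

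**3. When are events recorded?**

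| Period | Safety evaluation text | Table 1 |
|---|---|---|
| Weeks 1-12 (training) | recorded | marked |
| Week 13 (training end) | not covered | blank |
| Weeks 13-24 (follow-up) | not covered | marked |
| Week 25 (follow-up end) | not covered | blank |

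The two differ by the 12 follow-up weeks. The self-report diary row carries the same two marks, so the safety entry does not look like a stray one.

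**4. What the data could show (rates are assumptions).** Let n = 103 per group (protocol), r_T and r_C the proportions with a complaint in each group, and a the share of Tai Chi group complaints attributed to training.

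Recorded counts: Tai Chi = a × r_T × 103; control = 0. True excess = (r_T − r_C) × 103.

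With equal rates in both groups, the true excess is 0:
- 5%: 0.05 × 103 = 5.15. About 5 versus 5 occur; between 0 versus 0 and 5 versus 0 are recorded.
- 10%: 0.10 × 103 = 10.3. About 10 versus 10 occur; between 0 versus 0 and 10 versus 0 are recorded.
- 20%: 0.20 × 103 = 20.6. About 21 versus 21 occur; between 0 versus 0 and 21 versus 0 are recorded.

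One recorded result also fits opposite truths:
- Equal rates of 10%, all attributed: 1 × 0.10 × 103 = 10.3, recorded as 10 versus 0. True excess: 0.
- 20% versus 10%, half attributed: 0.5 × 0.20 × 103 = 10.3, recorded as 10 versus 0. True excess: (0.20 − 0.10) × 103 = 10.3.

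The assumed rates set the size of these counts but not the conclusion. The control zero holds at any rate.

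**The case against.** The strongest defence is that the trial's objective is effectiveness, safety appears in neither the primary nor the secondary outcome list, and a count of events attributed to Tai Chi is all that is wanted. If attribution were perfect, that count would itself be the number of events Tai Chi caused. This stands as far as it goes: the data can describe attributed events. But attribution of a single sprain cannot be verified, the count could not show that Tai Chi prevented any events, and Figure 1 does present safety as an outcome of a two-group trial.

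A reader might infer more than the documents support:
- *That unblinded staff decide what counts.* The protocol does not say so. It gives coaches and project managers the task of treatment and keeps them out of outcome assessment. What it supports is that no one is named to assess causation and that the staff closest to the events know the allocation.
- *That only musculoskeletal events are captured.* Every example is of that kind, but the list is open-ended. The term used for a lesion is vague rather than expressly limited.
- *That a misleading significance test is planned.* The Statistical analyses plan section names no safety comparison.
- *That the withdrawal criterion for serious adverse events fails in controls.* If the Safety evaluation definition governs that term, the criterion could operate only in the Tai Chi group. The protocol does not tie the two together, and sudden disease that prevents continuing is a separate criterion without a causality condition.
- *That such complaints are common among students.* The documents give no rate.

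**Conclusion.** The point holds in two parts.

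First, as defined, adverse events cannot be recorded in controls. The trial can report events attributed to Tai Chi but cannot estimate an excess risk over control. This rests on the wording of the definition and on the control group receiving no intervention, not on any assumed rate. The unnamed judge of causation makes the Tai Chi count harder still to interpret.

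Second, the Safety evaluation text (12 weeks) and Table 1 (weeks 1-12 and 13-24) contradict each other. The documents do not show which period is intended. This is a smaller matter and needs only reconciliation.

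Neither part affects the efficacy analyses. The first changes what data exist at the end of the trial, so it is more than missing detail and should be amended.

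**What to change.** - Define an adverse event as any untoward medical occurrence after randomisation, in either group, regardless of suspected cause.
- Record relatedness to Tai Chi as a separate field on the case report form, and name the role that completes it.
- Ask both groups the same question in the same way, through the diary that all participants already keep in both periods.
- Report counts by allocated arm, with the events judged related shown as a subset.
- Reconcile the recording period in Safety evaluation with Table 1, so that one period is stated in both places.

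The cost is a short amendment, one diary item and one form field, with a little more recording, mostly in controls. Because the withdrawal and reporting provisions use the same term, the sponsor should check that they still read as intended under the wider definition. This change concerns data capture and proposes no rule on withdrawal or treatment.

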**Exclusion criteria**

Students would be ineligible if they meet any condition as following:

①A long-term exercising TCC or other Tai Chi derived movements

②A member of Students' Wushu Association or Taekwondo Association or Aerobic Association or Dance Association.

③Severe cardiovascular disease or Musculoskeletal Disease

**Withdrawal criteria** Participants will be withdrawn from the trial if they present following conditions:

①Poor compliance (mean compliance < 85% at the last estimation) or noncompliance.

②Occurrence of a serious adverse event.

③Initiative exit.

④Unable to progress because of sudden disease.

⑤Members in the control group have been regularly engaged in the TCC exercise.

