**Ethical consideration**

This study protocol adheres to the principles of the Declaration of Helsinki and has been approved by the ethics committee of FJTCM (No. 042). The written consent will be obtained form each participants before the baseline assessment. All participants will have the right to withdraw from the study at any time.

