**Statistical analyses plan**

SPSS21.0 statistical analysis software will be used to analyze data. The primary outcomes of participants who are randomized and received at least one treatment week will be carried by the intention-to-treat (ITT) analysis. Per-protocol subjects analysis（PPS）of the primary outcomes will include participants who have completed the 24-week study without major protocol violations and have compliance rate > 85%. We will compare the results of the ITT with that PP analysis to check-up whether the results are consistent or not. The continuous variables will be expressed using means with standard deviations or medians with ranges. For the variables with a normal distribution, statistical comparisons between the groups will be made by using a *t* test. If the variables have a non-normal distribution of ordinal level, statistical comparison between groups will be made using the Mann-Whitney *U* test. Measures with a discrete distribution will be expressed as percentages and analyzed by theχ2 or Fisher’s exact test as appropriate. A general linear model or Logistic regression model will be applied to adjust the confounding influence if necessary. The *p* value is less than or equal to 0.05 will be considered as a test by the difference has statistical significance.

Participants’ recruitment

Eligible patients n=206

Baseline assessment

Exclusion (reasons): n=

Not meeting inclusion criteria: n=

Declined to participate: n=

Other reasons: n=

Randomization allocation

TCC training group

n=103

Control group

n=103

Drop out (reasons): n=

TCC training group: n=

Control group: n=

Outcome assessment after intervention: balance ability, lower limbs proprioception, flexibility, physical fitness, self-efficiency, psychological symptoms ,attention, stress, self-esteem, mood and mindfulness, quality of life, quality of sleep, safety outcomes.

Follow up for 12 weeks

Lost to follow up: n=

TCC training group: n=

Control group: n=

Outcome assessment after follow-up period

Included analysis: n=

TCC training group: n=

Control group: n=

Statistic analysis

Excluded from analysis: n=

TCC training group: n=

Control group: n=

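### The withdrawal rules take students out of the trial rather than out of training, and nothing keeps their week-13 and week-25 assessments

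*Protocol*

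**What the plan says.** The withdrawal criteria, printed under the Protocol's Exclusion criteria heading, open with "Participants will be withdrawn from the trial if they present following conditions". Five conditions follow: mean compliance below 85% or non-compliance, a serious adverse event, the student's own decision to leave, sudden illness, and regular TCC practice by a control student.

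Safety evaluation limits adverse events to those "defined as any functional lesion caused by the intervention, such as knee joint or ankle sprain, knee soreness, lumbar muscle strain" and similar. After treatment, each event is "immediately reported to the primary investigator and ethics committee to decide if the participant needs to withdraw the trial".

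The Statistical analyses plan section says that the primary outcomes of "participants who are randomized and received at least one treatment week will be carried by the intention-to-treat (ITT) analysis". The per-protocol set is "participants who have completed the 24-week study without major protocol violations and have compliance rate > 85" (percent). The two results are to be compared.

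Outcomes measurement and Table 1 schedule assessments at baseline, at the end of training (week 13 in Table 1) and at the end of follow-up (week 25). Neither says what happens to a student who has been withdrawn. Ethical consideration adds that "All participants will have the right to withdraw from the study at any time".

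**The concern.** Three different things are merged here: stopping the exercise, being unsuitable for the per-protocol set, and no longer being observed. Staff who follow the text would take a student with a serious event, an illness or poor attendance out of the trial, and nothing tells them to call that student back for the two later assessments. The ITT sentence says whose data are analysed. It does not ensure that those data are collected, and no statistical analysis plan can recover a balance test that was never done.

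The loss need not be even between arms. Only the TCC arm has a training programme to comply with, and only the intervention can cause an adverse event as Safety evaluation defines it. The injuries named there, such as sprains of the knee or ankle, plausibly affect balance and lower-limb proprioception, which are both primary outcomes. If such students go unmeasured, the remaining TCC arm may look better than the arm that was randomised.

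**Working it through.** **Which rule acts on which arm**

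- Compliance below 85%: mainly TCC, since controls are only asked to keep their usual lifestyle. Compliance itself is not defined.
- Adverse event under Safety evaluation: TCC only, by definition. Withdrawal is decided case by case.
- Serious adverse event: either arm, mandatory.
- Sudden illness: either arm, mandatory.
- Control student practising TCC: control only, mandatory.
- Student's own decision: either arm, and rightly ends participation.

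**How the compliance rule can catch an injury.** Assume that compliance means attendance over the whole programme. Five sessions a week for 12 weeks is 5 × 12 = 60 sessions, and 85% of 60 is 51. A student who misses two weeks (10 sessions) attends 50/60 = 83.3% and falls below the limit. The Protocol gives no attendance figures, so no rate follows from this.

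**Size of the shift**

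Inputs from Sample size estimation: mean ellipse area 531.25, SD 173.78, expected improvement 15%, 93 per group required, 103 per group recruited. The planned effect is 0.15 × 531.25 = 79.69 units.

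Assumptions not in the Protocol: a larger ellipse area means worse balance, and a lost TCC student would have been *d* = 0.5 to 1 SD worse at week 13 than the rest of that arm.

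Leaving *k* such students out of the 103 moves the TCC mean by (*k*/103) × *d* × 173.78:

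- *k* = 1: 0.84 to 1.69 units, or 1.1–2.1% of 79.69.
- *k* = 3: 2.53 to 5.06 units, or 3.2–6.4%.
- *k* = 10: 8.44 to 16.87 units, or 10.6–21.2%.

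The last line takes the whole allowance of 103 − 93 = 10 losses per arm, for any reason, and places it on TCC students with this deficit. It marks the scale and is not a forecast. The shift is near zero if injuries have healed by week 13.

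**Power.** With a two-sided 5% test (the Protocol does not state the sidedness), power is Φ(79.69 / (173.78 × √(2/*n*)) − 1.96). It is 90.8% at *n* = 103 and 87.7% if 10% of assessments are lost in both arms (*n* = 92.7). The loss of power is modest, so selective loss is the main issue.

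**The case against.** The strongest reply is that the text is milder than it looks. Safety evaluation provides treatment first and then asks whether withdrawal is needed, so remaining in the trial is an open outcome, and nothing suggests that a student with a sore knee would normally be removed. The mandatory rule for serious events is not tied to one arm. The assessment schedule does not exclude withdrawn students, and the ITT sentence points towards keeping their data. All of that stands. It limits the point to a gap in the wording and a risk of selective loss. It does not close the gap, because the only alternative the text gives to carrying on is to leave the trial, and no sentence directs that a withdrawn student be assessed.

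A reader might infer more than the Protocol supports in three places:

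- *That Figure 1 shows dropouts going unmeasured.* Its text lists "Drop out (reasons): n" ahead of "Outcome assessment after intervention: balance ability, lower limbs proprioception". The drawing is not available, the order is only that of the extracted text, and a count of dropouts does not say who was measured. This is weak evidence.
- *That the ITT and per-protocol comparison becomes empty.* It does not. A student measured at week 13 and lost later is in the ITT set but not the per-protocol set, so the two can still differ at week 13.
- *That the shifts translate into a higher false-positive rate.* If TCC does nothing for uninjured students, dropping the injured leaves an expected difference of zero and the chance of a false result favouring TCC stays at its nominal 2.5%. A higher rate needs a further condition: a true benefit in uninjured students that exactly offsets the injury harm, or worse balance beforehand in those who are injured. The Protocol supports neither.

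**Conclusion.** The point holds as a matter worth changing, at modest weight. The Protocol makes leaving the trial the consequence of serious adverse events, poor compliance and sudden illness, and a possible consequence of any adverse event caused by the intervention. It does not keep the later assessments that its own ITT set needs.

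The size cannot be determined, because the Protocol gives neither an injury rate nor a compliance rate. For adverse events alone it is probably small, at about 1–2% of the planned effect per TCC student lost. That figure rests on the assumed deficit of 0.5–1 SD still being present at week 13. The compliance rule may well remove more students than injuries do, but without a definition of compliance neither the number nor the direction of any bias can be fixed. The Protocol does not support a claim that every injured student is removed, or that the type I error is inflated by a stated amount.

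**What to change.** Amend the withdrawal criteria and Safety evaluation as follows:

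- Make adverse events (serious or not), poor compliance and sudden illness reasons to stop or pause TCC training, or to exclude the student from the per-protocol set, and not to leave the trial. For consistency, treat TCC practice by a control student as a reason for per-protocol exclusion only.
- State that every randomised student keeps the week-13 and week-25 assessments unless consent is withdrawn or the student is unable to attend or perform the test, and that the reason for any missed assessment is recorded.
- Leave the student's own right to withdraw unchanged.

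Both assessments are already in Table 1, so the cost is a change of wording and a little effort to bring back students who have stopped training. The limitation is that some injured students may be unable to do the balance test. Their missing values will remain, but with a recorded reason.

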**Statistical analyses plan**

SPSS21.0 statistical analysis software will be used to analyze data. The primary outcomes of participants who are randomized and received at least one treatment week will be carried by the intention-to-treat (ITT) analysis. Per-protocol subjects analysis（PPS）of the primary outcomes will include participants who have completed the 24-week study without major protocol violations and have compliance rate > 85%. We will compare the results of the ITT with that PP analysis to check-up whether the results are consistent or not. The continuous variables will be expressed using means with standard deviations or medians with ranges. For the variables with a normal distribution, statistical comparisons between the groups will be made by using a *t* test. If the variables have a non-normal distribution of ordinal level, statistical comparison between groups will be made using the Mann-Whitney *U* test. Measures with a discrete distribution will be expressed as percentages and analyzed by theχ2 or Fisher’s exact test as appropriate. A general linear model or Logistic regression model will be applied to adjust the confounding influence if necessary. The *p* value is less than or equal to 0.05 will be considered as a test by the difference has statistical significance.

Participants’ recruitment

Eligible patients n=206

Baseline assessment

Exclusion (reasons): n=

Not meeting inclusion criteria: n=

Declined to participate: n=

Other reasons: n=

Randomization allocation

TCC training group

n=103

Control group

n=103

Drop out (reasons): n=

TCC training group: n=

Control group: n=

Outcome assessment after intervention: balance ability, lower limbs proprioception, flexibility, physical fitness, self-efficiency, psychological symptoms ,attention, stress, self-esteem, mood and mindfulness, quality of life, quality of sleep, safety outcomes.

Follow up for 12 weeks

Lost to follow up: n=

TCC training group: n=

Control group: n=

Outcome assessment after follow-up period

Included analysis: n=

TCC training group: n=

Control group: n=

Statistic analysis

Excluded from analysis: n=

TCC training group: n=

Control group: n=

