**Methods/Design**

**Study design**

The study about the effectiveness of TCC on physical health and psychosocial well-being of college students is designed as a randomized, parallel controlled, assessor and statistician single-blinded trial. The allocation of participants will be equal (1:1) to the TCC exercise group (intervention group) and the control group. All assessment will be conducted by the blinded assessors at Fujian University of Traditional Chinese Medicine Affiliated Rehabilitation Hospital, and the gymnasium of FJTCM. The TCC exercise will be conducted at the gymnasium of FuJian University of TCM, and instructed by two qualified coaches. The entire trial program is illustrated in Figure 1.

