**Randomization and allocation concealment**

Participants will be randomly allocated to the TCC training group or the control group. Randomization will be performed at post-baseline assessment. The randomization list will be generated via Statistical Analysis System (SAS, version 9.1) by an independent non-investigator who works in Center for EBM of Academy of Integrative Medicine FuJian China. The allocation sequence will be concealed through a password access files which will be taken care of by the project manager. The eligible participants will be informed the allocated result by the project manager after post-baseline assessment.

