**Blinding**

It is impossible to blind the participants and TCC coaches in this trial. Nevertheless, we will assign a specified project manager to be in charge of the random allocated sequence and blind code of allocation in which TCC training group or control group will be replaced by the alphabet A or B. In addition, we will define each investigators a well-defined obligation; the project manager and TCC coaches will be not take part in the assessment of outcome; the outcome assessors and the statistic analyzer will be not involve in the participants’ recruitment and allocating. The allocation sequence and blind codes will be preserved hold by an independent project manager until the statistic analysis is completed.

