**Intervention**

**TCC training group**

Participants allocated to the TCC training groups will receive 12 weeks of TCC training. The TCC training will be instructed by two experienced TCC coaches, who have been qualified and engaged in the teaching of TCC course for at least 15 years. The 24 forms simplified TCC, which is recommended as the popularity health sport by General Administration of Sport of China, will be applied to members of the intervention group. Participants of TCC training group will be gathered to exercise at the campus gymnasium together. TCC training will be performed for 60 minutes per time and also include 10 minutes of warm-up (e.g., weight shifting, arm swinging, gentle stretches of the neck) at a frequency of five days a week. Participants will be taught the “meditation through movement” art of TCC, which includes the rationale states of TCC constitute, action essence of TCC, the TCM philosophy opinion of TCC, and deep breathing method. The instruction of TCC will be both verbal and visual. The systematic approach has been designed by two coaches and can be viewed on DVD.

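### The set labelled ITT requires a week of treatment, a condition undefined for untreated controls that on its most workable reading drops only TCC non-starters

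*Protocol*

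**What the plan says.** The Statistical analyses plan section of the protocol defines the main analysis of the primary outcomes as follows: "The primary outcomes of participants who are randomized and received at least one treatment week will be carried by the intention-to-treat (ITT) analysis". The only other set it names is a per-protocol set: 24 weeks completed, no major violations, compliance above 85%. The two results are to be compared for consistency. No analysis of all randomised participants is specified.

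The arms differ in what there is to receive:

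- TCC arm: "Participants allocated to the TCC training groups will receive 12 weeks of TCC training", in 60-minute sessions on five days a week.
- Control arm: "No specific exercise will be administered on the participants in control group", and "They will be informed to maintain their original lifestyle".

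On knowledge of allocation, the Blinding section says: "It is impossible to blind the participants and TCC coaches in this trial". The randomisation section adds: "The eligible participants will be informed the allocated result by the project manager after post-baseline assessment". Table 1 places randomisation in the two weeks before training begins.

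**The concern.** Intention-to-treat keeps the groups as randomisation formed them. Removing participants for something that happens after randomisation is harmless only if the removal is unrelated to allocation and to outcome. Excluding non-starters can sometimes be defended in a blinded trial with a comparable treatment in each arm, because the decision not to start cannot then depend on the arm.

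Neither feature is present here. One arm is asked to attend a class five days a week and the other is asked to change nothing, and each student knows which applies before week 1. Not starting can therefore reflect both allocation and motivation. Several of the seven primary outcomes (self-efficacy, SCL-90 symptoms, perceived stress) are questionnaires answered by students who know their arm, and motivation may well be related to those answers.

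The set carries every primary-outcome comparison, and a reader who sees the ITT label would assume that nobody was excluded. The planned consistency check does not help. The per-protocol set is also restricted after randomisation, and more tightly, so agreement between the two would not show that the exclusion was harmless.

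**Working it through.** **Step 1. What the condition does in each arm.** The protocol states no figure for this point, so the main check is to set the wording against the description of each arm. Three readings are possible.

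| Reading of the treatment-week condition | Controls | TCC arm |
|---|---|---|
| Literal: must have received the intervention | None qualifies, so there is no comparison | Those completing a week |
| Applies only where there is treatment to receive | All kept | Non-starters and week-1 leavers dropped |
| A week of the 12-week intervention period (Intervention regimen section) | Week-1 leavers dropped | Non-starters and week-1 leavers dropped |

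The first cannot be intended. The second is the most workable. The third is possible, but nothing in the protocol states it. None of the three gives all randomised participants.

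**Step 2. Size on the second reading.** Inputs from the protocol:

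- 103 per arm;
- SD of balance ellipse area 173.78;
- planned difference 15% of 531.25 = 0.15 × 531.25 = 79.69.

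The protocol gives no non-start rate and no outcome difference for non-starters, so these are assumed:

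- f = share of the TCC arm excluded;
- δ = absolute distance, in SD, between the excluded students' mean and the whole-arm mean.

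Removing that share shifts the TCC mean by fδ/(1 − f). With δ = 0.5:

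- f = 5% (0.05 × 103, about 5 students): 0.05 × 0.5 / 0.95 = 0.026 SD. On ellipse area, 0.0263 × 173.78 = 4.6 units, and 4.6 / 79.69 is about 6% of the planned difference.
- f = 10% (about 10 students): 0.10 × 0.5 / 0.90 = 0.056 SD. On ellipse area, 0.0556 × 173.78 = 9.7 units, or 12% of the planned difference.

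**Step 3. A wider range.** Let g be the difference in SD between those excluded and those retained. The shift is then f × g, which is the same quantity because g = δ/(1 − f). The error rates use a normal approximation with 103(1 − f) against 103 and no true effect.

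| f | g | Shift (SD) | Ellipse-area units | Share of 79.69 | Two-sided error at nominal 5% |
|---|---|---|---|---|---|
| 2% | 0.25 | 0.005 | 0.9 | 1% | 5.0% |
| 5% | 0.5 | 0.025 | 4.3 | 5.5% | 5.4% |
| 10% | 0.5 | 0.05 | 8.7 | 11% | 6.4% |
| 10% | 1.0 | 0.10 | 17.4 | 22% | 10.8% |

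**Step 4. Size on the third reading.** The bias is the TCC term minus the corresponding control term, f_T δ_T/(1 − f_T) − f_C δ_C/(1 − f_C), with each δ taken with its sign. It vanishes only if the two happen to cancel. An open-label trial that asks very different things of its two arms gives no reason to expect that.

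**The case against.** Four points on the other side deserve weight.

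- **The one-sidedness is not certain.** A reader might infer that the condition can exclude only TCC students. The protocol does not support that in full. It says "The intervention period in this trial will last 12 weeks" for the trial as a whole, and all participants keep diaries, so controls leaving in week 1 might be meant too. Figure 1 also has lines for control drop-outs and exclusions from analysis, without giving causes. What stands is that the condition is undefined for controls and one-sided on its most workable reading.
- **The direction is not shown.** A reader might infer that the bias must favour TCC. That needs early leavers to have worse outcomes, and no section says so. Students who decline could be busier, fitter or already active. The sample-size section also does not say whether a larger or a smaller ellipse area is the improvement, so the ellipse-area figures are absolute sizes and carry no sign.
- **The effect is probably small.** The sample-size section allows 10% for drop-out over the whole trial. Taking f = 10% spends all of that in week 1 of one arm, so the upper rows of the table are stretched. The figures also concern an instrument measured by blinded assessors. For the questionnaires, where concern is greatest, the protocol offers nothing to calculate from.
- **Rewording alone may change little.** The withdrawal criteria remove participants for non-compliance. If withdrawal also ends assessment, which the protocol does not clarify, a non-starter has no later outcome whatever the set is called.

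These limit the claim about size and direction and enlarge the fix. None makes the definition correct. Nor can it be excused as detail left to a separate analysis plan, because the protocol states the condition explicitly.

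**Conclusion.** The set is mislabelled and should be corrected. It conditions on treatment received, it has no stated meaning for controls, and no all-randomised analysis stands beside it. The resulting exclusion can depend on known allocation and so may bias the comparison, plausibly towards TCC if early leavers would do worse.

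The size is unknown and probably small: about 0.03 to 0.06 SD in absolute terms, if 5% to 10% of the TCC arm are excluded and differ by 0.5 SD from the arm mean. It is zero if nobody leaves before completing a week, or if those who leave resemble the rest. A reader might conclude that the randomised comparison is destroyed. That goes too far: the exclusion may involve only a handful of students, and the documents establish neither how many nor in which direction they would move the result.

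**What to change.** Three changes, made before any outcome data are seen:

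1. Define the ITT population as all randomised participants, analysed in the group to which they were allocated, regardless of sessions attended.
2. If a one-week set is still wanted, call it a modified set, say how the condition applies to controls, and use it only as a sensitivity analysis.
3. Reconcile the definition with the withdrawal criteria by separating withdrawal from training and withdrawal from assessment. Participants withdrawn for non-compliance should still be invited to the week-13 and week-25 assessments and be kept in the ITT analysis. Without this step the first change alters the label but perhaps not the data.

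The wording costs little. The real costs are a slightly diluted effect estimate and some extra effort to assess non-starters or handle their missing data. Made after the data are seen, the choice of set would look data-driven.
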